## Abstract

**Background:**

Advances in treatment have increased childhood cancer 5-year survival rates to greater than 80%. However, children previously treated with radiation are at significantly increased risk of developing subsequent neoplasms, the most common of which are skin cancers. The National Cancer Institute and Children’s Oncology Group have issued recommendations for survivors treated with radiation to perform monthly skin self-examinations and receive a physician skin examination at least annually, as early detection has demonstrated markedly improved outcomes in the diagnosis and treatment of skin cancers. The goal of the present study is to increase rates of skin self-examinations and clinical skin examinations among adult survivors of childhood cancer treated with radiation.

**Methods/Design:**

This randomized controlled trial uses a 3-group comparative effectiveness design comparing: (1) *Patient Activation and Education* (PAE) including text messaging, print and web-based tutorials over 12 months; (2) *PAE plus physician activation* (PAE + MD) adding physician activation/educational materials about survivors’ increased skin cancer risk and conducting full-body skin exams; and (3) *PAE plus physician activation, plus teledermoscopy* (PAE + MD + TD) adding participant receipt of a dermatoscope intended to empower them to photograph suspect moles or lesions for review by the study dermatologist.

**Discussion:**

The current study addresses barriers to screening in this population by providing educational and motivational information for both survivors and physicians regarding the value of periodic skin examinations. It also utilizes innovative mobile health technology to encourage and motivate (that is activate) survivors to conduct skin self-examinations, request physician exams, and obtain treatment when worrisome lesions are found. Finally, as a comparative effectiveness trial, this study isolates the effects of adding specific components to the patient activation intervention to test the most effective intervention for enhancing skin examination vigilance among this high-risk group.

**Trial registration:**

Clinicaltrials.gov: NCT02046811; Registration date: 22 January 2014.

## Background

Advances in diagnosis and treatment for children with cancer have contributed to an overall 5-year survival rate that currently exceeds 80% [1]. There are over 420,000 estimated survivors of childhood cancer in the United States [2]. In a study of 1,713 childhood cancer survivors using clinical evaluations, Hudson *et al*. found that 95% of these individuals experienced at least 1 chronic health condition by age 45 [3,4]. The late effects of the treatment of childhood cancer includes impaired growth and development, decreased or loss of fertility, organ dysfunction, cognitive impairment [2,5,6], and second neoplasms which occur in an estimated 20.5% of these individuals [7-11]. Among survivors receiving radiation treatment, the relative risk of developing a subsequent neoplasm is 2.7 (CI = 2.2 to 3.3). These neoplasms most frequently occur within the radiation field [8].

Skin cancers, primarily basal cell carcinomas (BCCs), are the most common subsequent neoplasm faced by childhood cancer survivors [8,12,13]. Approximately 20 years after receiving radiation therapy, when most of these patients are in their 30s, this population faces the prospect of multiple and recurrent skin cancers at rates much greater than that of an age-matched general population [8,12-14]. Adult survivors of childhood cancer under 35 who were treated with radiation have nearly a 40-fold risk for non-melanoma skin cancer and more than 2.5 times the risk of melanoma compared with the general population [13,15,16]. Delay of identification and diagnosis of skin cancer can result in unnecessary morbidity [17]. Most recent evidence indicates that earlier diagnosis of a BCC can lead to smaller tumors, potentially less extensive treatment, better outcomes, and lower treatment costs [18].

Because of the extraordinarily high skin cancer rates in this special population, in April 2012 (updated in April 2014), the National Cancer Institute released a PDQ® (evidence-based data summary) strongly encouraging the use of the annual dermatological exam to screen for early-onset skin cancer in childhood cancer survivors [19]. The Children’s Oncology Group also specifies in its long-term survivorship guidelines that survivors of childhood cancer who received radiation should check their skin monthly for changes and have a thorough skin examination by a health care provider at least once a year [20].

### Importance of early detection

Skin cancer and its precursors ‘writes their message in the skin for all of us to see’ and can be easily seen by the patient, their providers, and significant others [21-25]. Therefore, teaching skin self-examination and encouraging patients to alert their physicians to skin changes provides a key opportunity for education and early detection. In the general population, thorough skin self-examination (TSSE), although only practiced by 15% of subjects, reduced mortality due to melanoma by an estimated 60% in one major case-control study [26]. Physician diagnosis was associated with a markedly higher rate of thinner melanoma in Australia [27], and a nearly 50% reduction in melanoma mortality in a region in Germany compared with unscreened control populations from adjacent regions in Germany and all of Denmark [28].

The American Academy of Dermatology has recommended the practice of skin self-examination to detect new and or changing lesions [29]. Individuals are encouraged to perform skin self-examinations regularly (for example, monthly) using the ABCDE (Asymmetry, Border, Color, Diameter, Evolution) algorithm [30]. Individuals should also request periodic full-body skin examinations as a national study of physicians indicate that they are more inclined to screen when requested to do so by their patients [31]. Such practices are particularly meaningful for those at highest risk for skin cancer, such as individuals treated with radiation during childhood. However, previous studies have demonstrated that only 29% of survivors report that they have ever received a physician skin examination for cancer [32].

## Methods/Design

### Study objectives and specific aims

The objective of this randomized study, entitled Advancing Survivors’ Knowledge (ASK) About Skin Cancer, is to determine the impact of a 12-month Patient Activation and Education intervention focused on early detection of skin cancer and timely medical follow-up among childhood cancer survivors treated with radiation. Key components of the ASK intervention utilize innovative technologies to activate patients to conduct skin self-examinations, request physician exams, and obtain treatment when worrisome lesions are found.

The specific aims of this study are: (1) to determine the impact of a Patient Activation and Education (PAE) intervention with and without physician activation (PAE + MD) and teledermoscopy (PAE + MD + TD) on skin cancer early detection practices measured at 12 and 18 months; (2) to determine the impact of the intervention on time to diagnosis; and (3) to estimate the cost and cost-effectiveness of the intervention. The intervention will teach skin cancer early detection skills to survivors, connect them with health care resources, and prompt medical staff who see this population to perform clinical skin exams.

### Study participants

The study will be conducted using the cohort of the Childhood Cancer Survivor Study (CCSS), funded by NCI grant U24 CA55727 (Principal Investigator, [name]). This cohort includes participants from 50 states diagnosed with a childhood cancer between 1970 and 1986 before age 21 years. Participants have been recruited by 27 clinical sites in the United States (US) and Canada. As of 2007, there were 12,323 known living participants, 46% of the sample were female, median age was 36 years, 73% were under age 40 years, 88% were White, non-Hispanic, and 25% had at least a college education [33-35].

Eligibility criteria for the ASK study include: (1) current age of 18 years or older; (2) previously treated with radiation for childhood cancer; (3) having seen their primary care physician or oncologist in the previous 2 years or planning to do so in the next year; (4) having no personal history of a skin cancer diagnosis, (5) possession of a cellular phone that can receive text messages, and (6) access to a DermLite (3Gen, San Juan Capistrano, CA, USA) compatible smartphone or tablet. Informed consent will be obtained from each enrolled participant in the ASK study.

### Conceptual model

The ASK study is guided by the 13-item Patient Activation Measure (PAM) [36], which posits that activated patients are better prepared to participate in self-management activities. Patient activation is increasingly seen as central to achieving improvements in the quality of care, better health outcomes, and less costly health care service utilization. Activation involves 4 stages: (1) believing that taking an active role as a patient is important, (2) having the confidence and knowledge necessary to take action, (3) actually taking action to maintain and improve one’s health, and (4) staying the course even under stress [36].

Individuals with higher levels of patient activation are more likely to engage in preventive behaviors such as attending routine check-ups and undergoing screening [37]. Utilizing key aspects of the PAM framework, the ASK study intervention was developed to emphasize the importance of understanding one’s role in managing his/her health and having the knowledge, skills, and confidence to do so.

Since 2004, numerous cross-sectional studies and randomized controlled trials have found patient activation to be related to healthy behaviors, appropriate use of the health care system, consumer behaviors (for example, researching physician qualifications, preparing a list of questions for a doctor visit), and chronic care self-management [38-41]. In an intervention trial of chronic disease patients, Hibbard and colleagues found positive change in activation resulted in positive change in various self-management behaviors [42]. Similarly, in a web-based randomized controlled trial for adults with asthma, hypertension, or diabetes, Solomon and colleagues determined that an online intervention had both positive and significant effects on the patient activation levels of participants in the intervention group (specifically attitudes toward knowledge, skills, and confidence in self-managing health), noting their increased likelihood to adhere to recommended health care practices [43].

Evidence suggests that primary care providers can play an important role in increasing patient activation [38,44]. For example, one study found that patients who report that their provider helped them learn to monitor their condition, set goals, and/or set up an exercise program, were more activated than patients who did not have this experience [38]. In addition to patient activation, the ASK study includes a primary care activation component described below.

### Design overview

This randomized controlled trial uses a three-group comparative effectiveness design comparing (Figure 1):

**Figure 1 Fig1:**
[figure not shown]
**Study design overview for the three intervention arms.**

*Patient Activation and Education* (PAE), including text messaging, web-based educational content, and print resources;*PAE plus physician activation* (PAE + MD): adding physician activation/educational materials (web and print) targeted to identified primary care providers;*PAE plus physician activation, plus teledermoscopy* (PAE + MD + TD): adding participant receipt of a dermatoscope and instructions for use. Teledermoscopy is a potentially valuable resource that may reduce costs and increase efficiency for both patients and physicians by providing expert skin assessments remotely [45].

### Primary study outcomes

Primary study outcomes will be measured at baseline, 12- and 18-months and include the following: (1) at least 1 thorough skin self-examination completed by the patient in the 2 months prior to both the 12- and 18-month survey; (2) at least 1 physician skin examination prior to 18-month survey; and, (3) reduction of the time interval between the first finding of a suspect lesion and a diagnostic visit.

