## Procedures

### Eligibility screening

Participants of the CCSS cohort who received radiation for their childhood cancer and were not known to have a personal history of skin cancer are eligible to participate. Recruitment for the current intervention coincided with the release of the CCSS Follow-Up 5 (FU5) survey; therefore, FU5 is utilized as a recruitment screening tool. Individuals who fulfill the criteria listed above are sent the screening questions: (1) Have you been diagnosed with a skin cancer; (2) Have you seen a regular health care provider in the past 2 years, or do you plan to see one in the next year; (3) Do you have a mobile phone that can receive text messages; and, (4) Do you have access to a smartphone or tablet? Participants are eligible to participate in the ASK study if they answer ‘no’ to the first question and ‘yes’ to the remaining questions.

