**DermLite lens attachment by 3Gen.**

Another key element of the study is the development of the photo repository where participants in the PAE + MD + TD arm will upload DermLite photographs for review. Images can be uploaded from participants’ phones/tablets or the study website. When participants upload a photograph to the repository, they are asked a series of questions including: (1) date the photo was taken, (2) if they had previously submitted a photo of that particular mole, mark or spot, (3) location of the mole, mark, or spot (with a drop down menu of options to select from), and, (4) symptoms of the mole, mark or spot (with a drop down menu of options to select from). The photos will be reviewed by study staff to ensure acceptable quality and content before they are sent to the study dermatologist. The photographs will be reviewed by the study dermatologist and an individualized report and status will be generated for each photograph (for example, (a) morphology is suggestive of a benign lesion; (b) morphology is indeterminate and management will require evaluation and follow-up with a physician; (c) lesion has morphologic features suggestive of malignancy; and, (d) image is of insufficient quality - photograph needs to be retaken). The report will be sent to the corresponding participant’s physician. The participant will be instructed to contact his or her identified physician to receive the teledermoscopy report and to discuss follow-up measures.

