#### Reduced time interval

We used the following assumptions from the literature: mean wait time (time between call for appointment and actual appointment) of 38.2 days (95% CI = (35.4, 41.0) [49]. Based on the proportion of individuals with atypical moles and changing moles, we assume that for each of the study groups, there will be an estimated 60 to 75 participants per 267 in each group who will seek care from their primary physician or dermatologist in the 18-month period for a suspect skin lesion. A clinically significant improvement in reduction of time between the first finding of a suspect lesion and diagnostic visit would be between 14 and 21 days.

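### Primary outcome 3 starts its clock when a lesion is first noticed, with no link to randomisation, so as written it can include pre-trial delay

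*Protocol article*

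**What the plan says.** All references are to the protocol article.

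- **Outcome.** Primary study outcomes lists, as its third item, "reduction of the time interval between the first finding of a suspect lesion and a diagnostic visit". In the same sentence the first two outcomes are tied to survey dates. The third has no window and no stated relation to randomisation.
- **Entry.** The only skin-related criterion in Study participants is "having no personal history of a skin cancer diagnosis". The only skin-related question in Eligibility screening is "Have you been diagnosed with a skin cancer". Neither concerns a current lesion that has not been diagnosed.
- **Contributors.** Reduced time interval expects that "there will be an estimated 60 to 75 participants per 267 in each group" will contribute. It identifies them by seeking care during the 18 months, not by finding the lesion in that period.
- **Effect sought.** The same section says, in days: "A clinically significant improvement in reduction of time between the first finding of a suspect lesion and diagnostic visit would be between 14 and 21". Its reference wait is 38.2 days (95% CI 35.4 to 41.0), counted from the call for an appointment to the appointment.

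**The concern.** Take a participant who noticed a lesion six months before enrolment and shows it to a doctor in month 1. Under the definition as written, the recorded interval is about seven months, and six of those had passed before any arm could act. Randomisation should spread such people evenly among those enrolled, so the first consequence is noise: a few very long intervals in each arm, against a target difference of two to three weeks.

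The second consequence is possible bias. Only people who reach a visit contribute an interval, and the interventions act on that step. Physicians in Arms 2 and 3 are urged to do a full-body examination, and Arm 3 participants photograph suspect lesions. If these arms bring more long-standing lesions to a visit, their average recorded delay rises for a reason unrelated to how quickly new lesions are seen.

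**Working it through.** **The plan's own figure.** The article gives no power for the interval outcome. Its stated 85% (Power calculations) is for physician screening: 2-df chi-squared, n = 200 per arm, alpha 0.025. With noncentrality n·Σ(p − p̄)²/[p̄(1 − p̄)]:
- rates 30/30/45%: 200 × 0.015/0.2275 = 13.2, power 85.9%
- rates 30/45/45%: 200 × 0.015/0.24 = 12.5, power 83.7%

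The 85% is reproduced to within 2 points. It is unaffected by this point and says nothing about the interval.

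**Inputs from the article for the interval.** Difference 14 to 21 days; 60 to 75 contributors per arm; threshold 0.025 (two-sided critical value 2.24).

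**Assumptions, not in the article.** SD of the interval without pre-trial delay: 25 or about 38 days (the latter sets the SD equal to the reference mean). Share q of contributors whose lesion predates randomisation: 10 to 30%. Mean pre-trial delay D: 90 to 365 days. Arms are compared on means; the article names no test for this outcome.

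**Step 1. How large an SD the design can carry.** For 80% power, maximum SD = difference/[(2.24 + 0.84)·√(2/n)].
- 14 days: 24.9 (n = 60) to 27.8 (n = 75)
- 21 days: 37.3 (n = 60) to 41.7 (n = 75)

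**Step 2. Noise, fixed 180-day delay.** Base SD 38, q = 20% in both arms, n = 67, true reduction 18 days.
- Added variance: 0.2 × 0.8 × 180² = 5184
- SD: √(38² + 5184) = √6628 ≈ 81
- SE of the difference: 38 × √(2/67) = 6.6, rising to 81 × √(2/67) ≈ 14
- z: 18/6.6 = 2.7, falling to 18/14 ≈ 1.3, below 2.24

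**Step 3. Noise, exponential delay.** Variance = s² + 2qD² − (qD)², n = 60.

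| Base SD | q | D (days) | SD | Power, 14 days | Power, 21 days |
|---|---|---|---|---|---|
| 25 | 0 | – | 25.0 | 80% | 99% |
| 25 | 10% | 90 | 46.5 | 28% | 59% |
| 25 | 20% | 180 | 110.9 | 6% | 11% |
| 38.2 | 0 | – | 38.2 | 41% | 78% |
| 38.2 | 10% | 90 | 54.8 | 20% | 44% |

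Check of row 2: 625 + 2 × 0.1 × 8100 − 81 = 2164, and √2164 = 46.5.

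**Step 4. Bias if shares differ.** Bias = (difference in share) × D. The difference in share that cancels the sought effect is effect/D:
- D = 90: 15.6 points (14 days) or 23.3 points (21 days)
- D = 180: 7.8 or 11.7 points
- D = 365: 3.8 or 5.8 points

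A larger difference would change the sign. With equal shares the bias is zero.

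**The case against.** The strongest reply is that this is a journal article and the time origin may be fixed in a full protocol or analysis plan that is not shown. No sentence says outright that pre-trial delay is counted. That limits the claim to what follows from the wording. It does not remove the point, because the article itself defines this primary outcome and the entry criteria, and followed literally they admit such intervals.

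Other objections stand and narrow the point:

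- **Baseline data may exist.** The article says "Primary study outcomes will be measured at baseline, 12- and 18-months", and under Recruitment the baseline survey is completed before randomisation. Its items are not shown, so one cannot say that lesion status is not collected.
- **The upload questions prove nothing here.** A reader might infer from items such as "if they had previously submitted a photo of that particular mole, mark or spot" that the date first noticed is never asked. That list is introduced as open-ended, and it covers Arm 3 only, so it could not be the source for a three-arm outcome.
- **The planning number does not show prevalent lesions.** A reader might infer from "Based on the proportion of individuals with atypical moles and changing moles" that the 60 to 75 includes lesions present at entry. The text does not say so: having an atypical mole is not the same as having already found it suspect, and a mole may start to change during follow-up.
- **Direction is uncertain.** Every arm is prompted to self-examine and to ask for an examination, so old lesions can surface in all three. A benign teledermoscopy report could even reduce visits for long-standing moles in Arm 3.
- **The figures depend on a comparison of means.** A rank-based or median analysis would be less sensitive to a long tail.

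**Conclusion.** The point holds as a defect in a stated primary outcome definition: the interval is not anchored to randomisation, people with a known but undiagnosed lesion are eligible, and contributors are identified by when they seek care. Read as written, some intervals can include delay that no arm can influence.

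Added variance is the firm consequence. Its size cannot be fixed from the article; under the assumptions shown it ranges from a marked to a near-total loss of power. Bias is conditional on the arms differing in the share of long-standing lesions that reach a visit, which is plausible but not shown.

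A reader might go further and conclude that the effect will be cancelled or reversed, or that eligibility is wrong. The documents support neither. Cancellation needs an assumed imbalance between arms, and nobody needs to be excluded once the time origin is set.

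**What to change.** 1. Define the primary interval on lesions first found after randomisation.
2. For lesions already known at baseline, start the clock at randomisation and report them as a separate stratum.
3. Make sure that the pre-randomisation baseline survey records any current lesion of concern, or one under evaluation, with its site and when it was noticed. Make sure that the 12- and 18-month surveys record the date first noticed in all arms.

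Trial status says that recruitment was incomplete at submission, so these changes were still possible then for people not yet enrolled.

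**Cost.** A few survey items, one or two sentences of outcome wording, and fewer contributors than the 60 to 75 planned. As an example, dropping 20% of 60 leaves 48. With an SD of 25, power for 14 days is then Φ[14/(25·√(2/48)) − 2.24] = Φ(2.74 − 2.24) ≈ 69%. That compares with 80% at n = 60 with no pre-trial delay, and with 17% if that 20% stay in with a mean delay of 90 days (SD 59.5). If the SD is 38.2, power for 14 days is only 41 to 50% even with all 60 to 75 contributors, so anchoring the clock does not by itself make this outcome well powered.

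**What remains.** Finding a lesion after randomisation is itself affected by the intervention, so the arms may still differ in which lesions enter. The plan should acknowledge this.

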#### Arm 2: Patient Activation and Education plus physician activation

In addition to the PAE elements, participants’ physicians are mailed physician activation materials. The goal of the physician activation intervention is to increase provider knowledge about the importance of early detection for survivors, with a particular focus on this specific population, motivate these providers to educate and screen patients, and to provide them with the skills and confidence needed to perform clinical examinations. Provider intervention materials include: (1) an introduction letter describing the intervention and examination recommendations; (2) information about increased risk of skin cancer for adult survivors treated with radiation and the role of primary care in early detection and treatment; (3) instructions on how to conduct a full skin cancer examination; and, (4) access to the study website, with specific information for health care professionals that contains resources and images to assist in conducting skin exams and identifying potential skin cancers. Providers are also given access to the new web-based curriculum guide developed by the INFORMED study of skin screening for primary care physicians [46,47]. Physicians are provided with a study 1-800 number should they have questions regarding the examination or follow-up care or need help ensuring an expedited referral to a dermatologist from the American Academy of Dermatology.

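### The lesion-to-visit interval exists only for participants who find a lesion and attend a visit, so Aim 2 has no comparison protected by randomisation

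*Protocol article*

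**What the plan says.** The section on primary study outcomes lists, as its third item, "reduction of the time interval between the first finding of a suspect lesion and a diagnostic visit". The second specific aim, on time to diagnosis, depends on it.

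The section headed Reduced time interval sets out the planning. It expects that "there will be an estimated 60 to 75 participants per 267 in each group who will seek care from their primary physician or dermatologist" over 18 months, and applies the same range to every arm. It takes from the literature a "mean wait time (time between call for appointment and actual appointment) of 38.2 days". It then gives the target, in days: "A clinically significant improvement in reduction of time between the first finding of a suspect lesion and diagnostic visit would be between 14 and 21". It gives no power for this outcome, no test, no analysis set and no rule for a participant who finds a lesion and has no visit.

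On what the interventions are for, the study objectives say the key components should "activate patients to conduct skin self-examinations, request physician exams, and obtain treatment when worrisome lesions are found". The Arm 2 description says the physician materials, which Arm 3 also receives, should "motivate these providers to educate and screen patients". In Arm 3 only, a dermatologist reads uploaded photographs and may report a lesion as looking benign. The report goes to the physician, with referral encouraged where needed.

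**The concern.** Randomisation makes the arms comparable over all 267 participants in each. It does not make them comparable over the quarter or so who go on to find a lesion and attend a visit, if the intervention affects who those people are.

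Here it plausibly does. All arms receive the patient education, so that component is not a source of difference. Physician activation and teledermoscopy are the differences between arms. A prompted physician may find lesions or arrange visits that would not otherwise have happened. A participant with a dermatoscope may notice and pursue more lesions, or may be reassured by a read. Assuming equal care-seeking in every arm sits badly with the trial's own aims.

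What is at stake is the conclusion for Aim 2. An arm that brings in people who would never have attended could look slower because those people took longer. An arm in which fewer people attend could look faster or slower depending on whose visits are missing. The limitations in the Discussion cover recall, social desirability, the lack of a no-education control and under-documentation in charts. They do not mention this selection.

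**Working it through.** **The article's own figure.** The article states no power or sample size for the interval. Its one power figure, 85%, is for physician screening and reproduces: a 2-df chi-squared test with 200 per arm at 0.025 gives 85.9% for rates of 30/30/45% and 83.7% for 30/45/45%. Also 200/(1 - 0.25) = 266.7, so 267 per arm and 801 in total. Nothing below depends on that figure or changes it.

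**Inputs from the Reduced time interval section**
- Contributors per arm: 60/267 = 22.5% to 75/267 = 28.1%.
- Reference mean: 38.2 days. It runs from the call to the appointment, so it is only a stand-in for the interval from lesion discovery to visit.
- Target effect δ: 14 to 21 days.

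**Assumed, because the documents give no value**
- Arm 1 has 60 attenders averaging 38.2 days.
- Arm 3 has the same 60, each faster by δ, plus 15 people who would otherwise not have attended. That makes 75, the top of the planning range.
- The extra 15 average m days.

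**Formula.** Observed difference, Arm 3 minus Arm 1 (negative means Arm 3 is faster):

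[60(38.2 - δ) + 15m]/75 - 38.2 = -0.8δ + 0.2(m - 38.2)

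| m (days, assumed) | δ = 14 | δ = 0 |
|---|---|---|
| 38.2 | -11.2 | 0.0 |
| 60 | -6.8 | +4.4 |
| 90 | -0.8 | +10.4 |
| 120 | +5.2 | +16.4 |

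Worked case, δ = 14 and m = 60: (60 × 24.2 + 15 × 60)/75 = 2352/75 = 31.4, and 31.4 - 38.2 = -6.8 days.

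**Break-even.** The difference is zero when m = 38.2 + 4δ. That is 38.2 + 56 = 94.2 days for a 14-day effect and 38.2 + 84 = 122.2 days for a 21-day effect. Above those values the sign reverses.

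**Selection the other way.** Suppose there is no true effect and 15 of the 60 visits in Arm 3 do not take place. If those visits would have averaged 10 days, the difference is (2292 - 150)/45 - 38.2 = +9.4 days. If they would have averaged 60 days, it is (2292 - 900)/45 - 38.2 = -7.3 days.

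**Sensitivity to the baseline.** The shift from 15 extra attenders is 0.2 × (m - baseline). With an assumed baseline of 90 days and m = 120, it is 0.2 × 30 = 6 days.

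**The case against.** The strongest reply is that the article fixes an outcome, not an analysis. It names no analysis set and no summary measure, and an unseen analysis plan may handle non-attenders properly. Much of this stands, and it rules out several stronger readings that a reader might infer.

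- *That the plan compares mean days among care-seekers, or drops finders who never attend.* The only mean given is a literature waiting time, and the 60 to 75 is an expected count. Neither rule is written anywhere.
- *That Arm 3 would date the discovery of the lesion by its photograph.* The upload form does ask for the "date the photo was taken", but the tracking section uses repository data for photograph counts and report turnaround. No passage uses the photo date to start the interval.
- *That a benign read removes the visit in Arm 3.* Participants are told to contact their physician for the report and to discuss follow-up, with no exception for benign reads. Avoided visits are possible but not stated.
- *That the false difference matches the 14 to 21 day target.* Reaching 16.4 days needs a 120-day mean for the added group, no true benefit at all, opposite ends of the planning range in the two arms, and a baseline that measures a different interval. At 90 days the figure is 10.4, below the target range.

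The structure of the outcome remains. Even if non-attenders were censored, an analysis of lesion finders would still condition on finding a lesion, which happens after randomisation. The article defines no version of this outcome over everyone randomised. It is also fair to say that the sample size rests on the screening outcomes, which this point does not touch.

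**Conclusion.** The concern holds as a matter of definition. A named primary outcome exists only for a subset formed after randomisation, expected to be 22.5% to 28.1% of each arm, and the components being compared can change that subset. A difference in the interval alone cannot be read as an effect of physician activation or teledermoscopy.

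The size cannot be determined from the documents. A gap of 15 attenders between arms, within the planning range, would turn a true 14-day reduction into 6.8 days if the added group averaged 60 days and into 0.8 at 90. The sign would reverse only above 94.2 days. These means are assumptions and the 38.2-day baseline is a stand-in, so the arithmetic shows that the comparison could mislead, not that it will. This is an inexpensive improvement that changes what Aim 2 can conclude. It is not a flaw in the trial's sizing or in its screening outcomes.

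**What to change.** 1. Add, as the randomisation-protected analysis for Aim 2, the cumulative incidence by month 18 of a diagnostic visit for a suspect lesion, measured from randomisation in all randomised participants.
2. Report by arm the numbers who found a suspect lesion, had a teledermoscopy read and attended a visit.
3. Present the finding-to-visit interval as a supportive analysis and state that it is conditional and not a randomised comparison. Keep finders with no visit, censored at the 18-month survey. Date the discovery of the lesion by the same survey question in every arm.

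A time-to-event analysis among finders is not enough by itself, because it keeps the conditioning on finding a lesion. Treating a benign read as a competing event would not help either, since that event can occur only in Arm 3.

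The cost is mainly analysis wording. Visits are already to be collected by survey and chart review. Whether the surveys ask when the lesion was first noticed and why the visit took place cannot be seen here; if they do not, an item is needed. The real drawback is interpretive. The all-randomised measure is less direct than days of delay, and a lower visit rate in Arm 3 may reflect benign reads, so it must be read alongside the counts in item 2.
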